### 2.5. Procedure

The patients will be recruited according to the inclusion and exclusion criteria. Then, only patients without alterations in the electrocardiogram will be randomly assigned to one of five groups: auricular vagus nerve stimulation at 25 Hz frequency (atVNS) (*n* = 34); sham auricular vagus nerve stimulation (Sham atVNS) (*n* = 17); cervical vagus nerve stimulation at 25 Hz frequency (ctVNS) (*n* = 34); sham cervical vagus nerve stimulation (Sham ctVNS) (*n* = 17); axillary nerve stimulation at 25 Hz frequency (ANS) (*n* = 34). Pre-intervention baseline measures (FIQR, BPI, PSQI, and BDI) will be performed once a week for 3 weeks and before the first intervention day, resulting in four baseline measures (one per week) to evaluate the stability of the symptoms. Then, each participant will receive five 30 min consecutive sessions of stimulation (verum or sham) per week (one per day), for four weeks (in total, 20 sessions) over the left branch of the auricular or cervical vagal nerve or over the left axillary nerve, depending on the group. The patients will not be aware of the stimulation condition (verum vs. sham) within each group, and data analyses will be conducted by researchers not involved in the respective interventions, who will use numerical codes for each experimental condition in order to assure double blinding. Once the analyses have been conducted, the codes will be revealed. In the atVNS verum and sham groups, the anodal electrode will be positioned over the cymba conchae of the left auricle and the center of the left ear lobe, respectively, and the cathode (return electrode) over the antitragus. In the ctVNS verum group, the anodal electrode will be positioned on the surface of the throat that corresponds to the position of the left cervical branch of the vagus nerve, adjacent to the position of the cervical carotid artery (2 cm anterior to this branch for the sham ctVNS condition), and the cathode over the lower cheek. In the ANS verum group, the anode will be positioned over the left axillary nerve under the shoulder, and the cathode over the lower cheek. The positions of the electrodes for the respective procedures are shown in Figure 2.

The post-baseline outcome measures (FIQR, BPI, PGIC, PSQI, and BDI) will be recorded immediately after the fifth session of each intervention week, resulting in four intra-intervention measurements. Four additional post-intervention follow-up measures will be recorded to evaluate potential short- and long-lasting treatment effects, a week, a month, 3, and 6 months after the last intervention session, resulting in four intra-intervention and four post-intervention measurements. Although no conclusive evidence about tVNS effects on heart rate variability is available [69], heart frequency will be recorded before and after each tVNS session, the high-frequency/low-frequency heartbeat ratio will be calculated, and data will be correlated with the outcome measures. Pro-inflammatory cytokine levels taken from blood samples before the start of the intervention and immediately after 10 and 20 intervention sessions, as well as 1 week, and 1 month after the end of the intervention, will be analyzed as proposed biomarkers of the anti-inflammatory effects of the intervention [70]. To measure plasma cytokine levels, the enzyme-linked immunosorbent assay (ELISA) protocol will be used [71]. Plasma collection will be selected to optimize the yield of cytokines of interest (TNF α, IL-1β, IL-6) [72]. Within 1 h after collection, blood will be centrifuged for 10 min at 1300 g and 4 °C, and the supernatant will be transferred to a separate tube and then centrifuged for 10 min at 16,000 g and 4 °C. The resulting platelet-poor plasma will be stored in 0.5 mL aliquots at low temperatures (−80 °C) in order to maintain cytokine stability until the analysis. After each intervention, participants will be asked to guess the stimulation condition (real, sham, or unable to guess) for evaluation of successful blinding as previously reported [73], and any adverse effect of the stimulation or any aspect related to tVNS will be evaluated via an adapted standard questionnaire for assessment of adverse effects induced by a related non-invasive brain stimulation tool, namely, transcranial direct current stimulation (tDCS) [74], as a measure of the safety of the intervention. All sessions will take place at the aforementioned hospital. Figure 3 depicts the design of the study.

### 2.6. Statistical Analysis

To exclude differences of baseline measurements (BPI scores as primary outcome measure, and FIQR, PGIC, PSQI, and BDI scores as secondary outcome measures) between groups, a mixed model 4 × 4 ANOVA will be used, with one between-group factor with four levels (4 groups), and one within-subject factor (four baseline measurements). A mixed model 4 × 8 ANOVA, with one between-group factor with four levels (four groups) and one within-subject factor (8 measurement days), will be used to analyze the scores of the outcome measures obtained in each of the questionnaires throughout the study (intra-intervention and follow-up period). In case of significant results of the ANOVAs, exploratory Bonferroni-corrected post-hoc *t*-tests will be conducted. A univariate analysis by a Chi-square test will be performed to explore the success of blinding with regard to the intervention, and *t*-tests as well as Chi-square tests will be conducted to exclude demographic differences (gender, age, and years of education) between groups. Pearson’s correlation coefficient (Pearson’s *r*) will be calculated for each tVNS group to analyze possible correlations between vagal activity measures (heart rate variability) during the intervention and questionnaire scores (FIQR, BPI, PGIC, PSQI, and BDI), as well as between pre- and post-intervention pro-inflammatory cytokines levels and outcome measures. The critical level of significance for all statistical analyses will be set to *p* < 0.05. The analyses will be carried out using the SPSS statistical software package.

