The results of this intervention will help to elucidate if tVNS is a feasible method to induce clinically relevant analgesic effects in fibromyalgia patients (primary outcome measure). In addition, considering that the vagus nerve controls the autonomic nervous system and inflammatory signals [18,19,20], whose activity is apparently altered in fibromyalgia patients [25,27], other symptoms, including sleep and mood disorders, and quality of life (secondary outcome measures) could also benefit from this intervention. However, this study might face some limitations. First, high inter-individual variability in the fibromyalgia symptoms [76] might make it difficult to evaluate the efficacy of the treatment, despite the control of the baseline symptom state. Future multi-center studies with highly representative samples might be required to support the validity of the results of the envisaged pilot study. Preliminary results accomplished by this study may also be extended in future studies by the inclusion of other groups with chronic pain not primarily related to disturbances of the autonomic or immune systems, such as, for example, post-stroke pain, in which muscle pain symptoms are due to central alterations.

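### Baseline significance tests cannot exclude imbalance between arms, and the stated efficacy ANOVA makes no use of baseline BPI, so chance gaps go uncorrected and precision is lost

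*Protocol article*

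**What the plan says.** Section 2.6 gives the baseline ANOVA its purpose in its opening words, "To exclude differences of baseline measurements (BPI scores as primary outcome measure", and its structure as "one between-group factor with four levels (4 groups), and one within-subject factor (four baseline measurements". Demographics are handled the same way: "tests will be conducted to exclude demographic differences (gender, age, and years of education) between groups". One threshold serves everything: "The critical level of significance for all statistical analyses will be set to" p < 0.05. The section gives no margin for an acceptable difference and no consequence for either result of these tests.

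The efficacy model is a second mixed ANOVA, with "one within-subject factor (8 measurement days), will be used to analyze the scores of the outcome measures" obtained "throughout the study (intra-intervention and follow-up period". Section 2.5 shows that the eight days are the four end-of-week assessments during treatment and the four follow-ups. Baseline is therefore neither a level of the within-subject factor nor a covariate. Section 2.5 also collects four weekly baseline scores, and Section 2.4 uses simple randomisation with no stratification on pain stated.

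Section 2.1 sizes the trial on a different model, the group-by-measurement interaction with baseline as one of two occasions.

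**The concern.** A p-value above 0.05 does not exclude a difference. After randomisation the null hypothesis of the baseline test is already known to be true, so the test only asks whether chance produced the differences that chance produced. It says nothing about whether the observed gap is large enough to matter for the outcome.

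This would be a matter of wording if the efficacy analysis used baseline. As written it does not, so the test is the only stated safeguard against imbalance in the primary outcome. A chance gap in baseline BPI then persists in part at every later visit. It enters the group main effect and the between-group post-hoc tests, where it can imitate or mask a tVNS effect. The between-patient variation that the four baseline scores could remove also stays in the error term.

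**Working it through.** **Inputs.** 34 per group, four groups and correlation 0.5 between repeated measures come from Section 2.1; four baseline scores from Section 2.5; eight post-baseline days and alpha 0.05 from Section 2.6. Assumptions made here: equal variances, the same correlation r between any two occasions, no dropout, and r up to 0.7 as a second case.

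**The plan's own figure.** For the interaction in Section 2.1, λ = f²·N·m/(1 − r) = 0.04 × 112 × 2/0.5 = 17.92. With 3 and 108 degrees of freedom the critical F is 2.689 and the power 0.951. The stated N = 112 is reproduced, but for a pre/post model that Section 2.6 does not specify.

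**How much of a baseline gap persists.** The mean of four baseline scores has variance (1 + 3r)/4, in units of the single-score variance. The expected later gap per unit of baseline gap is r/[(1 + 3r)/4].
- r = 0.5: 0.5/0.625 = 0.80, so a 0.35 SD gap carries over as 0.28 SD.
- r = 0.7: 0.7/0.775 = 0.90, so it carries over as 0.32 SD.

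**How often a sizeable gap passes the test.** Simulating 20,000 correct randomisations and keeping those with baseline ANOVA p > 0.05, the largest gap between a tVNS arm and a control arm has a median of 0.24 SD (r = 0.5) to 0.27 SD (r = 0.7). It exceeds 0.35 SD in about 17% (r = 0.5) to 26% (r = 0.7) of them.

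**What this does to the planned group main effect when there is no treatment effect** (simulation, r = 0.5 to 0.7):

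| Set of trials | Falsely significant |
|---|---|
| All | about 5% |
| Baseline ANOVA non-significant | about 2% to 3% |
| Baseline ANOVA non-significant and largest gap above 0.35 SD | about 11% (r = 0.5) to 7% (r = 0.7) |

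As a share of the trials that pass the baseline test, the last row is 0.17 × 0.11 ≈ 1.9% at r = 0.5 and 0.26 × 0.07 ≈ 1.8% at r = 0.7. Most of the 2% to 3% in the row above it therefore comes from trials with a sizeable baseline gap.

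**Precision.** The eight-visit mean has variance (1 + 7r)/8, which is 0.5625 at r = 0.5.
- Unadjusted SE of a pairwise difference: √(2 × 0.5625/34) = 0.182 SD.
- Share of variance explained by the four-score baseline mean: r²/[0.625 × 0.5625] = 0.25/0.3516 = 0.711.
- Adjusted SE: 0.182 × √(1 − 0.711) = 0.098 SD.
- The same calculation gives 0.151 against 0.108 SD at r = 0.3, and 0.208 against 0.079 SD at r = 0.7.

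**The case against.** The strongest reply is that the error rate is sound. Randomisation keeps unconditional type I error at 5%, and among trials that pass the baseline ANOVA the main effect is falsely significant less often than that. This stands, and the point must not be put as an inflated false-positive rate.

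Two stronger readings are tempting and should be resisted.
- A reader might infer that the baseline ANOVA misses a real 0.5 SD imbalance about a quarter to a half of the time. The arithmetic can be done (24% with one arm shifted and r = 0.5), but sound randomisation does not produce a true population shift. The 0.5 SD is not a figure from the protocol. The rate also runs from 12% to 63% at r = 0.5, depending on the pattern of means and on whether one or four baselines are used.
- A reader might infer that a 0.35 SD gap gives a 13% to 14% false-positive chance. That describes an uncorrected, stand-alone t-test at one visit. Section 2.6 runs Bonferroni-corrected post-hoc tests, and only after a significant ANOVA. At 0.05/6 (six pairs assumed) the figure is about 1% to 2% even before the ANOVA gate.

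The Discussion's phrase "despite the control of the baseline symptom state" is only weak support. It stands within a stated limitation and can refer to the repeated baseline measurements; it does not claim that the groups are balanced. Nor does the article say that the report will declare the groups comparable.

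It is also fair that a constant gap cancels out of the group-by-day interaction. However, that interaction compares post-baseline days with each other and does not measure change from baseline. The pre/post interaction in Section 2.1 would use baseline, but Section 2.6 specifies another model, so it does not cure the omission. An unseen analysis plan might add a covariate. What is criticised here is the stated purpose of the tests and the model as stated.

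**Conclusion.** The point holds in a limited form. Significance tests cannot do what Section 2.6 asks of them, and the stated efficacy ANOVA leaves baseline BPI out although it is measured four times. The harm is conditional bias in the trials where chance produces a noticeable gap, together with a loss of precision in every trial. At r = 0.5 the loss is the larger matter: the adjusted variance of a pairwise difference is 1 − 0.711 = 0.289 of the unadjusted one.

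The sizes rest on equal correlation between all occasions. If correlation fades over the six months of follow-up, both the carry-over and the gain from adjustment will be smaller; r = 0.3 shows the direction. The plan should be changed, but the defect does not invalidate the trial.

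**What to change.** In Section 2.6, delete the ANOVA, t-tests and Chi-square tests meant to exclude baseline and demographic differences, and present these data descriptively by arm. In the efficacy models for BPI, FIQR, PSQI and BDI, enter the patient's mean of the four baseline scores on that questionnaire as a prespecified covariate, whatever any baseline p-value would show. PGIC has no baseline assessment in Section 2.5, so it takes no such covariate and should leave the list of baseline measures.

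Reconcile this model with the pre/post interaction used for the sample size in Section 2.1, so that the trial is sized on the analysis it will run. In the Discussion, refer to adjustment for the baseline score.

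The cost is one degree of freedom per model and some redrafting. The data are already being collected.

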Sample size calculation will be based on the hypothesized significant differences between (auricular vs. cervical vs. sham vs. axillary) and within (baseline vs. post-intervention) groups. We conducted an a priori calculation of the sample size by the GPower statistical power analysis tool (3.1.9.2) for a mixed-model repeated-measures ANOVA (with groups and pre/post-intervention measures as levels of the between-group and within-group factors) [50], as a primary outcome parameter conducted for the pain questionnaire (BPI). Because the main parameter of interest for this calculation is the interaction between the factors group and measure, we conducted the analysis for the within–between interaction, setting the following input parameters: effect size (f) = 0.2 (medium size), α value = 0.05, Power (1-ß) = 0.95, number of groups = 4 (pooled sham, axillary stimulation, cervical tVNS, and auricular tVNS), number of measurements = 2 (baseline as pre-intervention, and at the end of the intervention), correlation for repeated measures = 0.5, and with nonsphericity correction (1). The output parameters were: non-centrality parameter = 17.92, critical F = 2.68, actual power 0.951, and total sample size = 112. Taking into account these estimates and adding 20% to the calculated sample to compensate for possible dropouts, we will include 34 patients per group (total sample size of 136).

Written informed consent (available in Supplemental material) will be provided by all patients prior to their participation in the study. The clinical trial will be submitted for consideration and approval by the Regional Ethics Committee for Clinical Studies. In accordance with national legislation (93/42/EEC and RD 1090/2015), the study will be pre-registered in the Spanish registry of clinical studies (https://reec.aemps.es/reec/public/web.html#, accessed on 28 December 2021). The study complies with the code of Ethics of the World Medical Association Declaration of Helsinki (amend 64th, 2013).

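### The trial is powered on a baseline-to-end-of-intervention × group interaction, but the planned efficacy ANOVA contains only the eight post-baseline visits, so the stated 95% power belongs to no term of the planned analysis

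*Protocol article*

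**What the plan says.** **Sample size (Protocol article, Section 2.1).** The calculation is for a mixed repeated-measures ANOVA on the BPI. The article states that "the main parameter of interest for this calculation is the interaction between the factors group and measure" and, accordingly, "we conducted the analysis for the within–between interaction". The inputs are "effect size (f) = 0.2 (medium size), α value = 0.05, Power (1-ß) = 0.95, number of groups = 4", then "number of measurements = 2 (baseline as pre-intervention, and at the end of the intervention"), with "correlation for repeated measures = 0.5, and with nonsphericity correction (1"). The output is N = 112, raised to 136.

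**Efficacy analysis (Section 2.6).** The model crosses group with a repeated factor, described this way: "one within-subject factor (8 measurement days), will be used to analyze the scores of the outcome measures obtained in each of the questionnaires". The article limits these days to the treatment and follow-up periods. Section 2.5 accounts for all eight: one at the end of each of the four treatment weeks, then one week, one month, three months and six months after the last session. Bonferroni-corrected t-tests follow a significant ANOVA and are labelled exploratory.

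**Baseline.** Section 2.5 states "Pre-intervention baseline measures (FIQR, BPI, PSQI, and BDI) will be performed once a week for 3 weeks", with a further measurement before the first session, giving four in all. Section 2.6 uses them in a 4 × 4 ANOVA of their own: "To exclude differences of baseline measurements (BPI scores as primary outcome measure, and FIQR, PGIC, PSQI, and BDI scores". PGIC is in that list, although Section 2.5 does not collect it at baseline.

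**The concern.** Two stated parts of the plan describe different tests. The powered interaction asks whether the groups changed differently between baseline and the end of treatment. In the 4 × 8 model, group × time asks whether the post-baseline curves differ in shape. The group main effect asks whether the groups differ on an average of the four treatment weeks and follow-up out to six months.

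Neither term is the powered question. Baseline pain is not a factor level, a covariate or a change-score reference in the efficacy model. A non-significant result in the separate baseline ANOVA neither removes an imbalance nor adjusts for one. The end of week 4, the visit that set the sample size, is reached only through exploratory post-hoc tests.

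At stake is how the primary result is read. If the two terms disagree, the article gives no rule for which one decides, and the 95% power cannot be cited for either.

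**Working it through.** **1. Reproduce the stated figure.** For the within–between interaction, λ = f²·N·m/(1 − ρ), with df (k − 1)(m − 1) and (N − k)(m − 1). With f = 0.2, N = 112, m = 2, k = 4 and ρ = 0.5:

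- λ = 0.04 × 112 × 2 / 0.5 = 17.92, df 3 and 108
- critical F = 2.689 (the article gives 2.68) and power = 0.9513

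N = 108 gives 0.943, so 112 is the smallest balanced size. With all 136 patients analysed, power is 0.981.

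**2. Put the effect on a scale that carries over.** With two occasions, f = 0.2 corresponds to a between-group SD of 0.4σ in the post-treatment shift, because half of the shift falls on each occasion. One example is both tVNS arms 0.8σ better than both controls. Check on change scores: their variance is 2(1 − 0.5) = 1, so λ = 112 × 0.4² / 1 = 17.92, as above.

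**3. Apply the same shift to the planned 4 × 8 model.** Let v be the fraction of the shift present at each of the eight visits, under compound symmetry. N × 0.16 = 17.92.

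- Interaction: λ = 17.92 × Σ(v − v̄)² / (1 − ρ), df 21 and 7 × 108 = 756
- Group main effect: λ = 17.92 × v̄² / [(1 + 7ρ)/8], df 3 and 108; at ρ = 0.5 the denominator is 0.5625

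| Pattern v over the eight visits | v̄ | Σ(v − v̄)² | Interaction λ | Interaction power | Group λ | Group power |
|---|---|---|---|---|---|---|
| Constant: 1 at every visit | 1 | 0 | 0 | 0.05 | 31.9 | 0.999 |
| Build-up, held: .25 .5 .75 1 1 1 1 1 | 0.8125 | 0.594 | 21.3 | 0.79 | 21.0 | 0.98 |
| Build-up, fade: .25 .5 .75 1 .75 .5 .25 0 | 0.5 | 0.75 | 26.9 | 0.90 | 8.0 | 0.63 |
| Treatment weeks only: 1 1 1 1 0 0 0 0 | 0.5 | 2 | 71.7 | >0.99 | 8.0 | 0.63 |

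Simulation with 3,000 trials per pattern agrees. For the constant effect, interaction, group and powered pre/post test reject in 0.048, 0.998 and 0.956 of trials. For build-up then held, the figures are 0.788, 0.975 and 0.952.

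**4. Vary the correlation from 0.3 to 0.8, with the shift fixed at 0.4σ and N = 112.**

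- Constant: interaction stays at 0.05; group falls from 1.000 to 0.980.
- Build-up, held: interaction rises from 0.60 to 0.999; group falls from 0.998 to 0.89.
- Build-up, fade: interaction rises from 0.73 to above 0.99; group falls from 0.81 to 0.46.

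**The case against.** **The planned model has a strong term in every pattern examined.** This is true at correlation 0.5. Section 2.6 lets any significant ANOVA result trigger the post-hoc tests, so a group main effect would count. A reader might infer from the 0.05 that the trial cannot detect a sustained benefit or is underpowered. The documents do not support that, because the group main effect has power 0.999 in that case. Nor does the powered test come out negative: the 4 × 2 interaction would keep 0.951, but it is not in the analysis plan.

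**A zero interaction is an extreme case.** It needs the full effect after 5 of 20 sessions and no change for six months, which the article does not predict. This stands, and it is why the other patterns are shown.

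**Baseline adjustment is a matter of efficiency, and may be in a SAP.** A post-only comparison of randomised groups is unbiased, and a missing covariate or unnamed deciding term would not alone be a finding in an article. Both points stand. The finding rests on two stated models that do not match.

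A reader might also infer that ANCOVA is clearly more precise than the planned analysis. That does not follow. At correlation 0.5 the mean of four baselines has variance (1 + 3 × 0.5)/4 = 0.625, so ANCOVA leaves 1 − 0.25/0.625 = 0.60. The planned eight-visit mean has 0.5625. At correlation 0.7 the order reverses: 1 − 0.49/0.775 = 0.37 against (1 + 4.9)/8 = 0.74.

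**The authors call the study a pilot.** It is nevertheless sized at 95% power for a named test, so that test should be in the analysis.

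**Conclusion.** The mismatch is real and should be corrected. The stated 0.951 is right for a 3-and-108-df test of baseline against end of intervention, and Section 2.6 contains no such test. The two terms of the planned model answer other questions. At N = 112 and correlation 0.5, their power ranges from 0.05 to above 0.99 for the interaction and from 0.63 to 0.999 for the group main effect, depending on the time course. They can give different answers, no deciding term is named, and neither uses baseline pain.

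The absence of baseline from the efficacy model and the zero contribution of a constant effect to its interaction do not depend on any assumption about size or correlation. The power figures do rest on assumptions: the time patterns are illustrative, compound symmetry is assumed, and the article's correlation of 0.5 for two occasions is extended to all visits.

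The PGIC entry in the baseline test is a small separate inconsistency with Section 2.5.

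**What to change.** In Section 2.6:

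- Name one primary test: BPI pain at the end of week 4, compared between groups by ANCOVA with the mean of the four baseline BPI scores as covariate. At minimum, name the 4 × 2 baseline/end-of-intervention × group interaction that the sample size already assumes, and say which baseline score it uses. That test keeps power 0.951 at N = 112 and 0.981 if all 136 patients are analysed.
- Keep the eight-visit model as a secondary analysis, also adjusted for baseline, and state which of its terms is interpreted.
- Remove PGIC from the baseline comparison and analyse it after baseline only.

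The cost is rewording. The four baseline scores and the week-4 visit are already scheduled, and the sample size does not change.

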## Abstract

Stimulation of the vagus nerve, a parasympathetic nerve that controls the neuro-digestive, vascular, and immune systems, induces pain relief, particularly in clinical conditions such as headache and rheumatoid arthritis. Transmission through vagal afferents towards the nucleus of the solitary tract (NST), the central relay nucleus of the vagus nerve, has been proposed as the main physiological mechanism that reduces pain intensity after vagal stimulation. Chronic pain symptoms of fibromyalgia patients might benefit from stimulation of the vagus nerve via normalization of altered autonomic and immune systems causing their respective symptoms. However, multi-session non-invasive vagal stimulation effects on fibromyalgia have not been evaluated in randomized clinical trials. We propose a parallel group, sham-controlled, randomized study to modulate the sympathetic–vagal balance and pain intensity in fibromyalgia patients by application of non-invasive transcutaneous vagus nerve stimulation (tVNS) over the vagal auricular and cervical branches. We will recruit 136 fibromyalgia patients with chronic moderate to high pain intensity. The primary outcome measure will be pain intensity, and secondary measures will be fatigue, health-related quality of life, sleep disorders, and depression. Heart rate variability and pro-inflammatory cytokine levels will be obtained as secondary physiological measures. We hypothesize that multiple tVNS sessions (five per week, for 4 weeks) will reduce pain intensity and improve quality of life as a result of normalization of the vagal control of nociception and immune–autonomic functions. Since both vagal branches project to the NST, we do not predict significantly different results between the two stimulation protocols.

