Since fibromyalgia involves a dysregulation of the autonomic (high sympathetic tone) and immune (enhanced pro-inflammatory activity) systems [25,41], non-invasive tVNS is expected to improve the symptoms of fibromyalgia, including chronic, musculoskeletal, and generalized pain [42,43], through modulation of the vegetative and immune systems [44]. The main objective of this intervention study is to evaluate the effects of repeated sessions of tVNS on pain and other symptoms in fibromyalgia patients, comparing auricular and cervical tVNS protocols which have been probed in other pathologies [45,46,47,48,49]. According to the effectivity reported in these studies, we hypothesize that a multi-session auricular and cervical tVNS protocol carried out under safety standards will provide analgesic and therapeutic effects in fibromyalgia patients, in comparison with sham and axillary nerve stimulation controls, and secondarily will also normalize the autonomic (via heart rate variability) and immune (via pro-inflammatory cytokine levels) functions supposedly altered in this disease.

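### The 0.95 power belongs to the four-group omnibus interaction; the comparisons that answer the hypothesis (tVNS against sham and axillary stimulation) are left to gated, exploratory post-hoc tests with lower power

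*Protocol article*

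**What the plan says.** The Introduction (section 1) states the hypothesis: both tVNS protocols will have analgesic effects "in comparison with sham and axillary nerve stimulation controls". The Discussion and Conclusions add that the sham and axillary arms are there to show that any effect is specific to the vagus nerve. The Abstract says of the auricular and cervical arms that "we do not predict significantly different results between the two stimulation protocols".

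Section 2.1 powers a different quantity: "Because the main parameter of interest for this calculation is the interaction between the factors group and measure". Its inputs are "effect size (f) = 0.2 (medium size), α value = 0.05, Power (1-ß) = 0.95, number of groups = 4", with two measurements and "correlation for repeated measures = 0.5, and with nonsphericity correction (1"). Its outputs are "non-centrality parameter = 17.92, critical F = 2.68, actual power 0.951, and total sample size = 112". Recruitment is raised to 34 per group, 136 in total, to allow for dropout.

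Section 2.6 plans a 4 × 8 mixed ANOVA on the questionnaire scores. Group comparisons follow under a condition and with a label: "In case of significant results of the ANOVAs, exploratory Bonferroni-corrected post-hoc" t-tests. The number of comparisons in the Bonferroni correction is not given, and no tVNS-versus-control contrast is named as primary.

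**The concern.** The hypothesis concerns particular pairs in a particular direction. With four groups and two measurements, the interaction test has 3 degrees of freedom, and any departure from equal change can make it significant, including a difference between axillary stimulation and sham. It cannot by itself support a statement that tVNS beats its controls. The tests that can are run only if the ANOVA is significant, are corrected over an unstated number of pairs, and are called exploratory.

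Two things follow. The efficacy conclusion would rest on tests that the plan itself does not treat as confirmatory. And a reader who takes 0.95 as the chance of answering the main question will be too optimistic, because the trial can give a significant F without showing that either tVNS arm is better than sham.

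**Working it through.** **1. Reproduce the stated figure.** Inputs from section 2.1: f = 0.2, α = 0.05, 4 groups, m = 2 measurements, ρ = 0.5, sphericity correction 1, N = 112.
- λ = f² × N × m / (1 − ρ) = 0.04 × 112 × 2 / 0.5 = 17.92.
- Degrees of freedom are 3 and 108, so the critical F is 2.689 (the article prints 2.68).
- Power from the non-central F is 0.951, which agrees with the article.

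**2. Convert f to a difference between groups.** In this design the SD of the group mean changes is 2fσ = 0.4σ. The SD of an individual's change is σ√(2(1 − ρ)) = σ. The article gives no pattern of means. Assume that the two tVNS arms are equal (in line with the Abstract) and that the two control arms are equal (an inference from the Discussion, which describes the axillary nerve as unrelated to fibromyalgia symptoms). Each group then lies 0.4σ from the overall mean, and the tVNS-control difference is d = 0.8 SD of change. Check: 112 × 0.4² = 17.92, the same λ.

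**3. Power per tVNS-control pair.** Two-sample non-central t, two-sided (the article does not state sidedness), with non-centrality d√(n/2). This is 0.8 × √14 = 2.99 at 28 per group and 0.8 × √17 = 3.30 at 34 per group.

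| Pairs in the correction | 28 per group (planned completers) | 34 per group (no dropout) |
|---|---|---|
| 1 (unadjusted) | 0.84 | 0.90 |
| 4 (each tVNS arm against each control) | 0.66 | 0.77 |
| 6 (all pairs of four groups) | 0.60 | 0.72 |

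With six pairs, 0.95 per pair would need 60 evaluable per group (240 in total).

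**4. Simulate the whole procedure.** Same assumptions, 28 per group, six pairs, post-hoc tests only after a significant F on change:
- the F is significant in 95% of trials;
- a given tVNS-control pair is significant in about 60%;
- at least one of the four tVNS-control pairs is significant in 90%;
- both tVNS arms beat sham in 44%;
- the F is significant but neither tVNS arm is shown better than sham in about 19%.

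**5. Power if the contrasts are planned.** At 28 per group, with the two sham halves pooled:
- Auricular versus sham and cervical versus sham by Holm: about 0.80 to 0.82 per pair, depending on whether the error variance comes from the pair or from all four groups, and 0.88 to 0.89 for at least one.
- Both tVNS arms pooled against sham (56 against 28): non-centrality 0.8 × √(56 × 28 / 84) = 3.46, power 0.93.
- The same pooled contrast if only one site works: the mean difference halves to 0.4, non-centrality 1.73, power 0.40.

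**6. Precision for auricular minus cervical.** The 95% CI half-width at 28 per group is 2.005 × √(2/28) = 0.54 SD of change, about two thirds of the 0.8 SD assumed for tVNS itself.

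**The case against.** A reader might infer that 0.95 is wrong. It is not. The article assigns it to the interaction ("we conducted the analysis for the within–between interaction, setting the following input parameters"), and for that test it reproduces. The fault is that this is not the test of the hypothesis.

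A reader might also take 0.60 as the plan's power. It is conditional. The article states neither the pattern of means nor the number of pairs. Other patterns with f = 0.2 give 0.76 (one group apart from three) or 0.93 (two groups at the extremes, two midway) for the largest difference with six pairs, although they fit the stated hypothesis less well. The figure also uses pre/post change, as the sample size does, whereas the 4 × 8 ANOVA covers eight post-baseline measurements. If post-hoc tests compare means over those visits, with an assumed between-visit correlation of 0.5, power over six pairs is 0.89 for a constant 0.8 SD difference, about 0.60 for an average of 0.6 SD and 0.41 for 0.5 SD. Correcting over six pairs at each of eight visits would give 0.33, but nothing in the text says that 48 tests are meant.

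The Abstract's prediction about the two sites might be read as a plan to claim similarity from a non-significant test. The article says only that no significant difference is expected; it does not say that similarity will be concluded.

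The article calls the study a pilot with preliminary findings, and gate plus Bonferroni is conservative against false positives. An F driven by axillary versus sham would show up in the follow-up tests. These points soften the matter but do not remove it: the article also states an efficacy hypothesis, runs a formal 0.95 power calculation and says that the design will let an effect be attributed to the vagus nerve. Nor is this merely detail left to an analysis plan. The gate and the exploratory label are stated, and a plan naming confirmatory contrasts would contradict them.

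**Conclusion.** The concern holds in this form: the powered test and the hypothesis do not match, and the comparisons that address the hypothesis have only exploratory, gated status. The 0.951 is correct for the interaction and should not be called an error.

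The size of the gap depends on assumptions: two equal tVNS arms, two equal control arms, d = 0.8 on pre/post change and two-sided tests. On these, power per tVNS-control pair runs from 0.60 to 0.77 across four or six pairs and 28 or 34 per group. The 19% figure further assumes six pairs and 28 per group. Even an unadjusted pair reaches only 0.84 at 28 per group, so under this pattern no choice of correction brings a single pair to 0.95 at the planned number of completers.

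**What to change.** In section 2.6, name the tVNS-versus-control contrasts on BPI at end of treatment as the confirmatory tests, remove the omnibus gate for them, and state how multiplicity is controlled. Two workable options:

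- **By site.** Auricular versus sham and cervical versus sham by Holm, with the axillary contrasts next. Power is about 0.8 per pair and just under 0.9 for at least one, at 28 per group. Each site keeps its own test.
- **Pooled.** Both tVNS arms versus sham, power 0.93. The cost is that power falls to about 0.40 if only one site works, and in a fixed sequence that failure would block every later test.

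The choice is the sponsor's, but it should be made and justified before unblinding.

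In section 2.1, give the power of the chosen contrast next to the omnibus figure, with the assumed pattern of means. Label the remaining pairs secondary, and report auricular minus cervical with a 95% CI.

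This changes wording and one power statement. It needs no more patients or visits. The price is that the other comparisons lose any claim to confirmatory status.
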